## Abstract

**Background:**

Most smokers do not use smoking cessation (SC) services although it increases successful quits. Passive referral providing SC information to smokers is commonly used in SC studies. Little was known about active referral in the community setting. This study aims to motivate community smokers to quit by brief SC advice using a validated AWARD model (Ask, Warn, Advise, Refer and Do-it-again) that adjunct with active referral of smokers to various SC services in Hong Kong.

**Methods/Design:**

This is a single-blinded, parallel three-armed cluster randomized controlled trial (RCT) with two treatment groups of (1) brief SC advice using the AWARD model, active referral to SC services plus a referral card and a health warning leaflet (active referral group) and (2) brief SC advice using AWARD model and health warning leaflet (brief advice group) and a control group receives general very brief advice with a self-help booklet. A total of 1291 smokers will be recruited from 66 clusters (recruitment sessions) with 22 will be allocated to each of the two intervention and one control groups. SC ambassadors will be trained for delivering the interventions and conducting telephone follow-up. The primary outcomes are self-reported 7-days point prevalence (PP) abstinence at 3 and 6 months follow-up. Intention-to-treat principle and multi-level regressions will be used for data analysis.

**Discussion:**

This is the first RCT on assessing a model combining brief advice and active referral to SC services among community smokers. The results will inform the practices of SC services and intervention studies.

**Trial registration:**

NCT02539875 (ClinicalTrials.gov registry; registered retrospectively on 22 July 2015)

## Background

Smoking remains as a leading preventable cause of death and healthcare costs worldwide [1] and in Hong Kong (HK) [2]. Although the daily cigarette smoking prevalence in HK halved from 23.3 % in 1985 to 10.5 % in 2015 [3], smoking and second-hand smoke accounted for 16 % of the overall number of deaths (*n* = 43,397) in 2013 [4]. Smoking cessation (SC) is highly cost-effective when compared to other health interventions [5]. The World Health Organization MPOWER policy package of “offer help to quit” means proactive SC services are needed to encourage smokers to quit smoking [1]. Current clinical SC practice guidelines of 5As *(****A****sk*, ***A****ssess*, ***A****dvise*, ***A****ssist* and ***A****rrange)* also emphasizes assisting smokers to quit [6]. Most of current SC services use the passive method to recruit smokers that rely on smokers’ self-initiation to seek help, such as calling the quit-line or attending the SC clinics [7]. The impact (effect of SC multiple by the number of smokers covered) [8] of the SC services is limited as only 16 % of smokers seek SC services worldwide [1]. It is worth-noting that HK smokers’ awareness of the SC services has been reduced (70.3 % in 2012 vs. 59.1 % in 2015) and hence the prevalence of services usage among these smokers dropped as well (8.5 % vs. 5.0 %) [3]. This suggests SC services promotion may be sufficient but further increase of usage needs innovative intervention. Thus, smokers should be introduced with, motivated to use and be proactively referred to the service to increase its impact.

Referral intervention includes passive and active methods. Passive referral involves asking or encouraging the smokers to use the SC services (e.g. quit-line or clinics) by providing information sheet of the service [9]. Smokers have to contact the service providers by their own effort and often only a small promotion of smokers will do so. In contrast, active referral involves physicians or other healthcare professionals formally referring smokers (sending smokers’ information, mainly the contact method) to SC services via fax, mail or centralized computer system [9–12], which overcomes the barrier of self-initiation. Once the SC service providers receive smokers’ information, they would subsequently call the smokers for arranging further cessation interventions. The effect of active referral for SC may be larger than that of passive referral as most who were passively referred to SC services failed to call the quit-lines for assistance [13, 14]. Particularly, Borland et al. [10] reported that fax referring smokers to an evidence-based quit-line service doubled the quit rate of the standard in-practice general practitioner management at 12-month follow-up (12.3 % vs 6.9 %).

Evidence on the effects of active referral on smoking abstinence and SC services use were scarce [15]. Most of these studies were conducted in the clinical settings, which showed the feasibility of utilising centralized manpower and patients’ database for developing new models of SC services. However, it is less clear about the feasibility and effectiveness of active referral in the community setting, where accounts for the majority of the smokers who mostly do not actively seek SC services. Smokers in the community may be different to those who are attending the clinics regarding levels of addiction, quit attempts and intention [16, 17]. Unlike clinical settings, lengthy interventions are less feasible in the community setting and community smokers have no prior rapport with the interventionists. Thus, a brief on-site intervention model is more feasible and subsequent intensive intervention can be referred to current SC services.

Based on the established SC guidelines [18], we have refined the SC guideline and developed a brief validated SC intervention using AWARD model: *Ask, Warn, Advise, Refer and Do-it-again* for community smokers [19]. Short advice lasting for 30 s to 10 min was found to be feasible in the community setting [16]. While most of the previous studies only focused on the quit-line referral (only one clinic referral study is identified [15]), there is limited knowledge on the effectiveness of referral to various SC services including quit-line, clinics and traditional acupuncture treatments. This RCT aims to motivate smokers to quit using brief intervention (AWARD) and actively refer smokers to major SC services in HK.

## Methods/Design

### Overview of design

This is a single-blinded, parallel three-armed cluster RCT with 1291 smokers aged 18 or above will be recruited from the community (Fig. 1). Cluster randomization will be used based on the recruitment sessions (total 66 sessions) to assign participants to one of three conditions of (1) brief SC advice using AWARD model, active referral to current SC services plus a referral card and a health warning leaflet (active referral group); (2) brief SC advice using AWARD model and health warning leaflet (brief advice group); or (3) self-help booklet with general advices (control group). The trial will follow the CONSORT criteria [20].

**Fig. 1 Fig1:**
[figure not shown]
Study design. *Survey includes participants’ demographics (baseline only), smoking habits, past quitting history (baseline only), quitting progress, readiness and efficacy to quit and their knowledge about smoking are obtained at recruitment site as the baseline; and § biochemical validation includes exhaled carbon dioxide and saliva cotinine tests

### Subject inclusion and exclusion criteria

Inclusion criteria include (1) Hong Kong residents aged 18 or above; (2) smoke at least one cigarette per day for the past 3 months; (3) exhaled carbon monoxide (CO) ≥ 4 ppm; (4) intent to quit or reduce smoking [21]; (5) able to communicate in Cantonese (including reading Chinese) and (6) have a local phone number for follow-up. Smokers who meet the above criteria but are currently involved in other SC programs and/or mentally or physically unfit for communication will be excluded.

### Recruitment

Participants will be recruited over 3 months from 66 recruitment sessions in the community in all 18 districts in Hong Kong as in our previous “Quit-to-Win” project [19, 22, 23]. Public open places with high flow of smokers will be identified and these mostly include outdoor places near large shopping malls or housing estates. Booths containing SC and recruitment messages will be set up onsite to attract smokers. Well-trained SC ambassadors will actively recruit the smokers who are near or attending the booths. The SC ambassadors are trained university students (mainly from the fields of nursing, public health, science and social sciences) and volunteers from the non-governmental organizations (NGOs). The SC ambassadors have to attend a two-day workshop in which they learnt the basic knowledge on smoking, tobacco control, SC services, skills on recruitment and intervention delivery. We will adopt “a-foot-in-the-door” approach [24] by asking the smokers their interests on participating in the SC trial. Smokers who showed interests will be assessed for eligibility and informed consents will be sought. The study has been approved by the Institutional Review Board of the University of Hong Kong/Hospital Authority Hong Kong West Cluster (UW15-332) and registered at ClinicalTrials.gov (NCT02539875).

### Cluster randomization

All participants recruited in a particular recruitment activity will be allocated to one of the 3 RCT groups. Individual randomization will not be used as the risk of intervention contamination at each site is high. Cluster randomization will be used to ensure the number of recruitment activities for the three RCT groups is similar. Sixty-six recruitment activities will be randomly assigned to any one of the three RCT groups by randomly generating blocks of 3, 6 or 9. The investigator will generate a list of random numbers in each block using Microsoft Excel. The list of random numbers will be assigned to a list of group assignment in which the first, second and third tertile will be as the active referral, brief advice and control groups respectively. A co-investigator who is not aware of allocation group will subsequently sort the random number in each block and that will be the group assignment sequence of the recruitment activities.

### Blinding

The RCT is single-blinded that all outcome assessors are not aware of the group assignment of the subjects.

### Sample-size calculation

The sample size calculation is based on the primary outcome of self-reported 7-day PP quit rate at the 3-month follow-up. Based on the previous similar studies conducted in the community in Hong Kong, the 3-month quit rate for the control group was approximately 10.0 % [19, 22, 23]. According to the RCT of active referral conducted by Borland et al. [10], the rate ratio of quit rate for the intervention and control group was 1.92 (intervention group: 12.3 %, control group: 6.9 %). Therefore, the effect size for the intervention in this study is set conservatively at 1.60. The quit rate for the intervention group (a combination of active referral and brief advice groups) versus the control group is 16.0 and 10.0 % respectively. To detect a significant difference of quit rate between intervention and control groups with a power of 80 and 5 % significance level, we will need 284 subjects per group. Assuming an intra-cluster correlation coefficient as 0.005 and retention rate of 70 % at the 3-month follow-up, the total sample size taking into account in the intra-cluster correlation within each recruitment session and attrition is 1291.

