### Outcome assessments

#### Primary outcome

The primary outcomes are self-reported 7-days PP quit rate at 3-month and 6-month follow-up. Subjects reporting not smoking in the past 7-days at 3-month and 6-month will be regarded as abstinence from smoking.

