### Data analysis

The main comparisons will be the self-reported 7 days PP quit rate among groups, which include: (1) Active referral plus brief advice vs. control: to test the bulk model of active referral with referral card plus brief counselling using AWARD model with smoking harms and cessation leaflet intervention effects; (2) Brief advice vs. control: to test brief counselling using AWARD model with smoking harms and cessation leaflet intervention effects; and (3) Active referral vs. brief advice: to test active referral with referral card intervention effects.

The intention-to-treat (ITT) principle will be used for outcome comparison between groups. Information missed at follow-up will be considered as non-quitters, non-reducers or do not use SC service if no records from the service providers are available for verification. Methods to handle missing cases (multiple imputations or complete case analysis) will depend on the proportion of actual percentages of the attrition rate. Baseline characteristics and outcome measures among groups at each endpoint will be compared using chi-square tests, Mann–Whitney tests and *t*-tests. Logistic regression will be used to predict quitting and models will be adjusted for baseline differences if necessary. Multi-level analysis method will be used to handle clustering effects.

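### The stated 80 % power belongs to pooled interventions versus control at 3 months, while the main comparisons are three single-arm contrasts at two primary time points

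*Protocol article*

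**What the plan says.** **Sizing (Sample-size calculation).** The calculation is "based on the primary outcome of self-reported 7-day PP quit rate at the 3-month follow-up". The contrast is the "intervention group (a combination of active referral and brief advice groups) versus the control group", at 16.0 % and 10.0 %. The section continues: "with a power of 80 and 5 % significance level, we will need 284 subjects per group". The inflation follows: "Assuming an intra-cluster correlation coefficient as 0.005 and retention rate of 70 % at the 3-month follow-up", giving 1291 in total. Whether the 5 % is one- or two-sided is not stated.

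**Endpoints (Primary outcome).** "The primary outcomes are self-reported 7-days PP quit rate at 3-month and 6-month follow-up". Neither time point is ranked above the other.

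**Comparisons (Data analysis).** Three main comparisons are listed:
- (1) active referral plus brief advice against control, explained there as a test of the bundled package;
- (2) "Brief advice vs. control: to test brief counselling using AWARD model" and its leaflet;
- (3) "Active referral vs. brief advice: to test active referral with referral card intervention effects".

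The abstract gives 22 clusters to each of the three arms. Table 1 shows that only the active referral arm receives the referral and the card.

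**The concern.** The contrast that was sized and the contrasts that will be tested are not the same. Pooling two arms against one gives the intervention side twice the subjects, so power computed for the pool overstates the power of one arm against control at the same difference. For comparison (3) no difference between the two active arms is assumed, and nothing is sized at 6 months.

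Two misreadings follow if this stays. A null result in a pairwise test could be taken as the result of a trial with 80 % power for that test. And with three comparisons at two time points and none put first, the article leaves open which result carries the primary conclusion.

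**Working it through.** **Inputs.** From the Sample-size calculation: 16 % and 10 %, 80 % power, 5 % level, 284 per group, intra-cluster correlation 0.005, retention 70 %, total 1291. From the abstract: 66 clusters, 22 per arm.

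**1. The plan's own total.** 3 × 284 = 852 evaluable. 852/66 is about 13 per cluster, so the design effect is 1 + (13 − 1) × 0.005 = 1.06. Then 852 × 1.06 / 0.70 = 1290.2, rounded up to 1291. So 284 is the evaluable number per arm.

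**2. The plan's 284.** For a group of size n with rate p1 against a group of size kn with rate p2:

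n = [zα·√(p̄(1 − p̄)(1 + 1/k)) + zβ·√(p1(1 − p1) + p2(1 − p2)/k)]² / (p1 − p2)², with p̄ = (p1 + k·p2)/(1 + k).

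| Calculation | One-sided 5 % | Two-sided 5 % |
|---|---|---|
| 1:1, one arm vs control | 388 | 492 |
| 2:1, intervention doubled (as in the plan) | 297 | 379 |
| 2:1, control doubled (reversed) | 284 | 359 |

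The exact 284 appears one-sided with the double-sized group on the control side: p̄ = 0.12 and [(1.645 × 0.398 + 0.842 × 0.424)/0.06]² = 284.0. With the doubling on the intervention side, the one-sided figure is 297, or 288 by the arcsine formula and 270 with unpooled variance. No two-sided or 1:1 version comes near 284. The number is therefore a one-sided, 2:1 pooled calculation.

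**3. Power at the planned size.** Per arm, 1291/3 = 430.
- Retained basis: 430.3 × 0.70 = 301 per arm; cluster size 13.7; design effect 1.063; effective n = 283.3.
- All-randomised basis: 430 per arm; cluster size 19.6; design effect 1.093; effective n = 393.8. This assumes that 16 % and 10 % still hold with missing counted as smoking.

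Power = Φ{[|p1 − p2|·√n − zα·√(p̄(1 − p̄)(1 + 1/k))] / √(p1(1 − p1) + p2(1 − p2)/k)}.

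- Pooled contrast, retained, two-sided: p̄ = 0.14; (1.0098 − 1.96 × 0.4250)/0.3965 = 0.446; power 67 %.
- One arm vs control, retained, two-sided: p̄ = 0.13; (1.0098 − 1.96 × 0.4756)/0.4737 = 0.164; power 57 %.
- One arm vs control, all randomised, two-sided: (1.1906 − 1.96 × 0.4756)/0.4737 = 0.546; power 71 %.

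| Contrast | Retained, two-sided (one-sided) | All randomised, two-sided (one-sided) |
|---|---|---|
| Pooled, 16 % vs 10 % | 67 % (78 %) | 82 % (89 %) |
| One arm vs control, 16 % vs 10 % | 57 % (68 %) | 71 % (81 %) |
| Active vs brief, illustrative 18 % vs 14 % | 25 % (36 %) | 33 % (45 %) |

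The 18 % and 14 % are an illustration that keeps the pooled mean at 16 %; the document gives no split. If both arms quit at 16 %, there is no difference to detect.

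**4. Why the all-randomised basis is optimistic.** If 16 % and 10 % are rates among responders and 30 % are lost and counted as smokers, the analysed rates are 0.7 × 16 = 11.2 % and 0.7 × 10 = 7.0 %. Then p̄ = 0.091 and (0.042 × √393.8 − 1.96 × 0.4067)/0.4057 = 0.089, giving 54 % two-sided.

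**5. Six tests, if unadjusted.** Three pairwise z-tests at two time points were simulated under no effect anywhere (2 million draws, two-sided 5 % each). The correlation between 3 and 6 months is an assumption, as the document gives none.

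| Correlation | 0 | 0.4 | 0.6 | 0.8 | 0.9 |
|---|---|---|---|---|---|
| Chance of at least one false positive | 22.9 % | 21.9 % | 20.5 % | 18.4 % | 16.7 % |

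The three tests at one time point alone give 12.2 %.

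**The case against.** **Comparison (1) may be the pool.** Its label resembles the sample-size wording, and then the sized test would be planned after all. But its explanation describes the package with referral and card, which by Table 1 only the active referral arm receives, so arm against control is the better reading. On the pooled reading the stated power still covers one test of six. The ambiguity stands as wording to reconcile.

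**The shortfall is not all due to unpooling.** This stands. On retained subjects the drop from 80 % to 57 % two-sided splits into about 13 points from sidedness and allocation (80 to 67) and about 10 from unpooling (67 to 57). One-sided, with all 430 per arm analysed at undiluted rates, a single arm against control just passes 80 %.

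**Stronger readings that the article does not support.**
- A reader might infer that 80 % is claimed for active referral against brief advice. The sample-size section ties its power to intervention against control and claims nothing for comparison (3).
- A reader might take comparison (3) as the trial's central question. The abstract and Discussion present the combined model as the subject, which is comparison (1).
- A reader might conclude that the trial has a familywise error near 20 %. The 5 % is stated only as a sizing input, and this is a condensed article whose analysis plan is not shown; a multiplicity rule may sit there. The absence of one here is not the finding.

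**Conclusion.** The concern holds as a mismatch within the article. The 80 % belongs to a contrast that, on the better reading, is not among the main comparisons, at one of two primary time points. An unseen analysis plan could rank the tests, but it could not make the published power statement fit the published comparisons.

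For one arm against control at 16 % and 10 %, power is about 57 % two-sided (68 % one-sided) on retained subjects. It is about 71 % (just over 80 % one-sided) if all 430 per arm are analysed with the rates undiluted. Comparison (3) and the 6-month time point were not sized. These figures rest on the document's intra-cluster correlation of 0.005, 70 % retention and equal arms.

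The 17–23 % familywise error is conditional on six unadjusted two-sided tests and an assumed correlation of 0 to 0.9. It is a consequence to guard against, not an established property of the trial.

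**What to change.** - Name one listed comparison and one time point as the primary test. The natural choice is active referral against control at 3 months, two-sided 5 %: it tests the combined model and uses the time point that was sized.
- Make the other comparisons and the 6-month time point secondary, or test them in a pre-specified order. Several orders are valid; it matters that one is fixed before outcomes are seen.
- Reword comparison (1) so that it cannot be read as the pool.
- Replace the pooled 80 % with the power of each pairwise comparison at the planned size. State sidedness, show both the retained and the all-randomised basis, and say that comparison (3) and 6 months were not sized.

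**Cost.** Wording only, with no added recruitment. The stated power will be lower, and later comparisons may lose a formal claim. For scale, 80 % two-sided for one arm against control needs 492 evaluable per arm. That is 1476 × 1.06 / 0.70, or about 2236 in total at the same design effect, and more if the 66 sessions become larger.

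### The 284 per group for 80 % power needs an unstated one-sided 5 % test; read two-sided, the same calculation gives about 67 %, and the quoted 1.92 should be 1.78 as a rate ratio

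*Protocol article*

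**What the plan says.** All of this is in the Sample-size calculation section of the protocol article, apart from the allocation.

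- Endpoint: "The sample size calculation is based on the primary outcome of self-reported 7-day PP quit rate at the 3-month follow-up".
- Control rate: "the 3-month quit rate for the control group was approximately 10.0" %.
- Comparison: "The quit rate for the intervention group (a combination of active referral and brief advice groups) versus the control group is 16.0 and 10.0 % respectively".
- Result: "with a power of 80 and 5 % significance level, we will need 284 subjects per group". Whether the test is one- or two-sided is not said.
- Inflation: an intra-cluster correlation of 0.005 and 70 % retention bring the total to 1291.
- Source of the effect: for the cited active-referral trial, "the rate ratio of quit rate for the intervention and control group was 1.92 (intervention group: 12.3 %, control group: 6.9" %). From this the text concludes that "the effect size for the intervention in this study is set conservatively at 1.60".

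The abstract gives the allocation: "66 clusters (recruitment sessions) with 22 will be allocated to each of the two intervention and one control groups". The combined comparison is therefore 2:1 in favour of intervention.

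The Data analysis section lists pairwise contrasts among the main comparisons, including brief advice against control, and counts participants missing at follow-up as non-quitters.

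**The concern.** A reader who meets a 5 % significance level with no qualifier takes it as two-sided. For 16 % against 10 % at 80 % power, a two-sided test needs far more than 284 per group, so either the number or the power does not follow from the stated inputs. The enrolment target of 1291 is built on 284 and carries the problem with it.

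The cited ratio can be checked within its own sentence: the two rates given do not divide to 1.92.

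The stake is how a null or borderline result is read. A trial described as having 80 % power has a 20 % chance of missing the assumed effect. If the real chance is nearer 33 %, a negative finding says less than the protocol implies, and less again for the comparison of a single arm with control.

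**Working it through.** **Inputs.** Control p0 = 0.10, intervention p1 = 0.16, difference 0.06; power 80 % (z = 0.8416); 5 % level (z = 1.6449 one-sided, 1.9600 two-sided); equal arms, hence 2:1 for the combined comparison; ICC 0.005; retention 70 %; 66 sessions.

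**Formula (pooled variance).** With k intervention subjects per control and p̄ = (p0 + k·p1)/(1 + k):

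n(control) = [z_α·√(p̄(1−p̄)(1 + 1/k)) + z_β·√(p0(1−p0) + p1(1−p1)/k)]² / 0.06²

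**Step 1. Reproduce 284.**

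| Test | Ratio (intervention : control) | Control | Intervention |
|---|---|---|---|
| One-sided | 1:2 (reversed) | 567.98 | 283.99 |
| One-sided | 1:1 | 388 | 388 |
| One-sided | 2:1 (real) | 297 | 594 |
| Two-sided | 1:2 (reversed) | 718 | 359 |
| Two-sided | 1:1 | 492 | 492 |
| Two-sided | 2:1 (real) | 379 | 758 |

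The exact match is the first row: (1.6449 × 0.3980 + 0.8416 × 0.4236)² / 0.0036 = 283.99. With the real 2:1 ratio, other one-sided formulas come near: 288 controls (arcsine) and 270 (unpooled). Two-sided at 2:1, the arcsine formula needs 366 controls, the unpooled 343, and the log-odds-ratio and log-risk-ratio formulas 401 and 414. None gives 284.

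**Step 2. Reproduce 1291.** 3 × 284 = 852. With 852/66 = 12.9 per session, the design effect is 1 + 11.9 × 0.005 = 1.06, and 852 × 1.06 / 0.70 = 1290.2, which rounds up to 1291. The inflation is consistent and treats 284 as evaluable subjects per arm.

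**Step 3. Power at 284 control and 568 intervention.** p̄ = (28.4 + 90.88)/852 = 0.14; standard error 0.02522 under no difference and 0.02353 under the assumed difference.

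- One-sided: (0.06 − 1.6449 × 0.02522)/0.02353 = 0.79, power 78.4 %. Arcsine gives 79.5 %, unpooled 81.7 %.
- Two-sided: (0.06 − 1.9600 × 0.02522)/0.02353 = 0.45, power 67.3 %. Arcsine gives 69.5 %, unpooled 72.3 %.

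**Step 4. One intervention arm against control, 284 each, same rates.** Standard errors 0.02822 and 0.02811: (0.06 − 1.9600 × 0.02822)/0.02811 = 0.17, two-sided power 56.6 %.

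**Step 5. All 1291 analysed, missing counted as non-quitters.** Session size 1291/66 = 19.56; design effect 1 + 18.56 × 0.005 = 1.093; effective size per arm (1291/3)/1.093 = 393.8. Two-sided power:

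| Meaning of 10 % and 16 % | Rates analysed | Combined 2:1 | Pairwise |
|---|---|---|---|
| Already missing = non-quitter rates | 10.0 vs 16.0 % | 81.7 % | 70.7 % |
| Completer rates, diluted by 0.70 | 7.0 vs 11.2 % | 63.8 % | 53.6 % |

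**Step 6. The cited ratio.** 12.3/6.9 = 1.78. Rounding of the two rates allows 12.25/6.95 = 1.76 to 12.35/6.85 = 1.80. The odds ratio from the same rates is (0.123/0.877)/(0.069/0.931) = 1.89, and up to 1.92 with rounding.

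**The case against.** The strongest reply is that the text never claims a two-sided test. Under a one-sided 5 % reading, the three usual formulas give 78 to 82 % with the real allocation, so the stated 80 % is met within about two points. The Data analysis section does not say its tests are two-sided either. This stands as far as it goes: the defect is an undisclosed one-sided calculation. Two-sided is the normal reading of an unqualified 5 % level, but it is a convention and not something the article states.

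A second reply is that the planned analysis keeps all 1291 participants, which lifts combined two-sided power to about 82 % if the assumed rates already count missing participants as non-quitters. That is correct under that assumption. The article does not say which kind of rate it used, and with completer rates the same analysis has about 64 %.

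Three stronger readings are tempting and not supported:

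- **That the allocation ratio was entered upside down.** The 283.99 match makes this plausible, but the article states no such ratio and a one-sided test with the correct ratio comes close. It also matters little: 80.0 % against 78.4 %.
- **That the 1.92 invalidates the sample size.** The calculation uses 10 % and 16 %, a ratio of 1.60, so 284 does not depend on it.
- **That 1.60 is not conservative at all.** It remains below 1.78; the margin is only narrower. The benchmark concerns active referral, while half of the combined group receives none, but how far that weakens the assumption is a judgement the article's figures cannot settle.

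**Conclusion.** The point holds in this form. The 80 % power with 284 per group rests on a one-sided 5 % test that the article does not disclose. On the calculation as written, with 284 evaluable per arm after clustering and attrition, two-sided power is about 67 % for the combined comparison (67 to 72 % across the pooled, arcsine and unpooled formulas) and about 57 % for one intervention arm against control if that arm also reaches 16 %. Two-sided 80 % for the combined comparison would need about 379 evaluable per arm, 1137 in all.

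A reader might infer that the trial simply has 67 % power. The article does not support a single figure: with all 1291 analysed, the combined comparison lies between about 64 % and 82 % and the pairwise one between about 54 % and 71 %, depending on what the 10 and 16 % represent. These figures take the stated ICC as correct, and the lower ones assume 70 % retention in every arm.

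The ratio of 1.92 is wrong as a rate ratio for the rates beside it. It may be an odds ratio or an adjusted estimate under the wrong label; the article cannot settle which.

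**What to change.** Revise the sample-size paragraph, leaving enrolment at 1291:

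1. State a two-sided 5 % level, and that the combined comparison is 2:1, intervention to control.
2. State whether 10 % and 16 % are completer rates or rates with missing counted as non-quitters.
3. Restate the power of 1291 on that basis for both the combined and the pairwise comparisons. On the calculation as written this is about 67 % and 57 %; Step 5 gives the values when all participants are analysed.
4. Reconcile 1.92 with the quoted 12.3 % and 6.9 %: give 1.78 as the rate ratio, or label 1.92 as the measure it actually is. If 1.60 is still called conservative, let the reader see that the comparison is with 1.78.

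This changes wording only; recruitment, conduct and analysis are untouched. The price is a less favourable stated power, unless the assumed rates prove to be missing = non-quitter rates, in which case only the pairwise power falls clearly short of 80 %.
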